### Patient Recruitment and Procedure

Eligible patients and their parents will be informed about the study by phone and, if interested, receive the patient information folder (PIF) by email. Participation will be voluntary and all data will be anonymized. Both parents will be asked to provide written informed consent. Patients who are 12 years old will also be asked to provide written informed consent themselves. Children under 12 years old will give their permission orally.

After informed consent is provided, children will be randomly allocated to the VRE intervention (N=100) or CAU (N=100) group at hospital admission. Randomization will be stratified by age group (4- to 7- or 8- to 12-years-old), and type of surgery (ie, oral and maxillofacial surgeries, tonsil and adenoidectomy, tympanostomy tubes, or other ear surgeries). The researchers and operating staff will be blinded to group allocation. The research assistant will not be blinded, since he/she will be guiding the intervention. This will take place in a separate room, in the presence of an accompanying parent. Un-blinding takes place if patients are excluded from the study and after the final assessment of the last included patient.

Assessments will be carried out at the following time points: (1) T1, admission to the hospital, before possible intervention; (2) T2, after the VRE intervention or after CAU, in the holding area; (3) T3, during induction of anesthesia, in the operating room; (4) T4, postoperatively, in the recovery room; and (5) T5, 3 days after surgery, at home.

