### Sample Size

To conduct a repeated measures analysis of variance (ANOVA) with 4 time points (ie, T1, T2, T4, and T5) for self-reported child anxiety, Cohen *f* of 0.25, an alpha of .05 (2-tailed), and a power of .85, a sample size of 200 patients is needed (100 patients per group). To perform regression analyses with 6 predictor variables, a small to medium effect size, and a power of .85, a sample size of 100 patients in the intervention group is sufficient.

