### Outcome Measures

An overview of the study design and variables at each time point are provided in Figure 5. The primary outcome is change in child state anxiety level between baseline (T1) and induction of anesthesia (T3), evaluated by a psychologist trained in the administration of the modified Yale Preoperative Anxiety Scale (mYPAS) [20,21]. The mYPAS is a commonly used observational tool consisting of 27 items divided into 5 domains: activity, emotional expressivity, state of arousal, vocalization, and use of parents.

Multiple secondary state anxiety outcomes will be examined. Children will indicate their level of anxiety with a Visual Analogue Scale (VAS) at different time points (T1, T2, T4, and T5) [22]. Moreover, situational parental anxiety, both pre- and postoperatively will be self-reported using the state anxiety form (20 items) of the State-Trait Anxiety Inventory (STAI) at T1 and T3 [23,24]. Either the psychologist (T1 to T3) or the recovery nurse (T4) will assess parental anxiety with the VAS.

Postoperative pain will be reported with 3 different instruments. The revised Faces Pain Scale (FPS-r) is a self-report measure designed for children to indicate pain intensity [25]. This measure will be used at T4 and T5. A recovery nurse, trained in administering the Face, Legs, Activity, Cry, and Consolability (FLACC) scale, will assess pain intensity at T4 [26,27]. This scale assesses nonverbal indicators of pain. The Parents’ Postoperative Pain Measure (PPPM) will be completed by parents at T5 [28].

Emergence delirium will be measured with the Pediatric Anesthesia Emergency Delirium (PAED) scale by the recovery nurse at T4 [29,30]. Finally, information regarding use of analgesics and healthcare use will be extracted from medical records.

Several factors associated with situational anxiety will be assessed because these may influence the efficacy of the VRE. Putative predictors are socioeconomic status, age, sex, type of surgery, preoperative child, and parental trait anxiety. Child trait anxiety will be assessed by parents with the Child Behavior Checklist (CBCL) at T1 [31]. Parental trait anxiety will be self-reported using the trait anxiety form (20 items) of the STAI.

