### Statistical Analyses

To examine the effect of the intervention on the primary outcome, a repeated measures ANOVA will be conducted with child state anxiety level at T1 (baseline state anxiety) and T3 (anxiety during induction of anesthesia) as within variables and group (VRE versus CAU) as between variables.

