**Figure 5 figure5:**
[figure not shown]
Flow chart of the study design with outcomes, instruments, and informants at each time point.

For the secondary outcome measures, repeated measures ANOVA will be conducted with situational parental anxiety at T1 and T3 as within variables and group as between variables. Also, repeated measures ANOVAs will be performed using postoperative pain at T4 (in the recovery room) and T5 (at home) as outcomes, with group as between variables. The effect of the intervention on emergence delirium at T4 will be examined with an analysis of covariance (ANCOVA). Age and sex effects will be accounted for in all analysis.

Multiple linear regression analyses will be performed with change in child state anxiety between T1 and T3 and change in pain between T4 and T5 as outcomes. Predictor variables (ie, socioeconomic status, age, sex, type of surgery, preoperative child, and preoperative parental trait anxiety) will be included into the linear models to identify which factors influence VRE efficacy.

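### Type of surgery is a stratification factor, but the stated adjustment for the VRE versus CAU comparisons is age and sex, so some precision may be lost

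*Protocol article*

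**What the plan says.** Three parts of the Methods bear on this.

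- **Allocation** (Patient Recruitment and Procedure): "Randomization will be stratified by age group (4- to 7- or 8- to 12-years-old), and type of surgery". The surgery categories are "oral and maxillofacial surgeries, tonsil and adenoidectomy, tympanostomy tubes, or other ear surgeries", so there are 2 × 4 = 8 strata.
- **Group comparisons** (Statistical Analyses): the primary model has child anxiety at T1 and T3 as within-subject levels "and group (VRE versus CAU) as between variables". Parental anxiety and pain get similar repeated measures ANOVAs, and emergence delirium an ANCOVA. The adjustment for all of them is given in one sentence: "Age and sex effects will be accounted for in all analysis".
- **Predictors** (Outcome Measures): "Putative predictors are socioeconomic status, age, sex, type of surgery, preoperative child, and parental trait anxiety". These variables "will be included into the linear models to identify which factors influence VRE efficacy". The Sample Size section sizes that regression work with the statement that "a sample size of 100 patients in the intervention group is sufficient".

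**The concern.** The design balances the arms on type of surgery, and the article treats surgery type as possibly predictive. The stated analysis of the group effect nevertheless carries only one of the two stratification factors (age), plus sex, which is not one. The predictor regressions do contain surgery type, but they look for factors that influence VRE efficacy and are sized on the intervention group. They do not estimate VRE versus CAU.

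Balanced stratified allocation removes between-surgery variation from the true sampling variance of the group difference. A model without the factor leaves that variation in the residual, so the reported standard error describes a less precise trial than the one that was run. At stake are intervals wider than they need be, tests that run below the nominal 5%, and some power.

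**Working it through.** **Inputs from the article.** 100 children per arm; two-sided alpha 0.05; power 0.85; "Cohen *f* of 0.25"; four surgery categories; two age groups.

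**Assumed, because the article gives no figure.** R² is the share of variance in the analysed contrast explained by surgery type, taken as 0, 0.05, 0.10 and 0.20. Arms are assumed balanced within strata.

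**1. The plan's own figure.** For a group-by-time F test with 4 time points, λ = N·f² = 200 × 0.0625 = 12.5, df1 = 3 and df2 = 3 × (200 − 2) = 594. Power is 0.854, so N = 200 reproduces. Nothing below changes it.

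**2. Which contrast matters.** With two time points, the group-by-time test is the comparison of mean T1 to T3 change between arms. A surgery effect on anxiety level that is constant over time cancels from the change. For the primary outcome, R² therefore refers to variance in change only. Emergence delirium is measured once, at T4, and pain only at T4 and T5, so no preoperative value removes a surgery effect on level from these outcomes.

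**3. Formulas.** Scale the outcome to SD 1, with nominal SE = √(2/100) = 0.1414. Under balanced stratified allocation the true SE is 0.1414·√(1 − R²), while the model without surgery type still reports about 0.1414.

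- SE overstatement = 1/√(1 − R²)
- Actual type I error = 2·[1 − Φ(1.96/√(1 − R²))]
- Power without surgery type = 1 − Φ[(1.96 − d/SE)/√(1 − R²)]
- Power with surgery type = 1 − Φ[1.96 − (d/SE)/√(1 − R²)]

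The reference effect is d = 0.426 SD, about what 100 per arm detects with 85% power. Then d/SE = 0.426/0.1414 = 3.012.

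**4. Results.**

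| R² | SE overstated by | Type I error without surgery type | Power without | Power with | Forgone |
|---|---|---|---|---|---|
| 0 | 0% | 5.0% | 85.4% | 85.4% | 0 |
| 0.05 | 2.6% | 4.4% | 86.0% | 87.1% | 1.1 points |
| 0.10 | 5.4% | 3.9% | 86.6% | 88.8% | 2.2 points |
| 0.20 | 11.8% | 2.8% | 88.0% | 92.0% | 4.0 points |

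Worked line for R² = 0.10: √0.90 = 0.9487 and 1.96/0.9487 = 2.066, so type I error is 0.039. Power without is 1 − Φ(−1.052/0.9487) = 1 − Φ(−1.109) = 0.866. Power with is 1 − Φ(1.96 − 3.175) = 0.888.

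**5. Simulation check.** 200 children, permuted blocks of 4 in the 8 strata, age and sex already in the model, d = 0.424, 4,000 runs per scenario. The block size and the mix of surgeries are assumptions.

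| R² | Mean model SE, without vs with | Type I error, without vs with | Power, without vs with |
|---|---|---|---|
| 0 | 0.138 vs 0.138 | 5.5% vs 5.5% | 85.8% vs 85.8% |
| 0.05 | 0.138 vs 0.134 | 4.6% vs 5.1% | 86.7% vs 87.5% |
| 0.10 | 0.138 vs 0.131 | 3.9% vs 5.1% | 87.7% vs 90.1% |
| 0.20 | 0.138 vs 0.123 | 2.8% vs 5.0% | 89.0% vs 93.6% |

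The two methods agree. Including surgery type when it explains nothing cost no power.

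**The case against.** The strongest reply is that the loss is conditional and may be close to nil where it matters most.

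- **Primary outcome.** In a simulation where surgery type affected anxiety level but not change (6,000 runs), the model SE was 0.141 with or without surgery type and type I error was 5.4% in both. The article says the listed factors may be associated with situational anxiety; it does not say that surgery type predicts change. This stands: the same table row cannot be applied to every outcome, and the primary may sit at its low end.
- **Allocation method.** The type I figures need near-balance within strata, as blocking gives. The article does not describe blocks. With simple randomization inside strata and R² = 0.20, the simulated type I error was 4.8%, not 2.8%. This stands as a stated assumption. Adjustment would still add precision in that case.
- **Condensed article.** The covariate sentence does not expressly exclude other terms, and a fuller plan might add them. This carries less weight. The article is not silent: it names a covariate set, applies it to all analyses, and names surgery type where it means to use it.

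A reader might also infer that the power gained by stratifying is thrown away. The figures do not support that: without surgery type, power at R² of 0.05 to 0.20 is 86.0% to 88.0%, still above the 85.4% at R² = 0. Only the further gain is forgone.

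**Conclusion.** The point holds as a matter of precision. The article stratifies on type of surgery, calls it a putative predictor, and leaves it out of the stated adjustment for every VRE versus CAU comparison. The size runs from nothing at R² = 0 to a standard error about 12% too large, a type I error of 2.8% and about 4 points of power forgone at R² = 0.20. It rests on two things the article does not give: how much variance in the analysed contrast surgery type explains, and balance within strata. The loss is plausibly larger for postoperative pain and emergence delirium than for the primary outcome.

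It would go too far to say that the standard errors are wrong for all outcomes, or that the trial's conclusions are threatened. The estimate is not biased, any error in the test is in the conservative direction, and N = 200 is unchanged. The change is still worth making, because it follows the trial's own design and costs almost nothing.

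**What to change.** In Statistical Analyses, add type of surgery as a four-level factor, in the categories used for randomization, to each VRE versus CAU comparison, alongside the planned age and sex. In the repeated measures ANOVAs include its interaction with time, because a main effect alone does not remove surgery-related variance from a group-by-time test. In the emergence delirium ANCOVA the factor itself is enough.

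This point does not call for a baseline covariate in the primary model: T1 is already a within-subject level there, so adding it would change the model.

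The cost is 3 degrees of freedom. With group, age (one linear term) and sex fitted, the residual goes from 200 − 4 = 196 to 193. No new data are needed, since surgery type must be known to randomize, and the sample size stays the same.

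### The predictor regression uses T4-to-T5 change in pain to study VRE efficacy, but both times follow the intervention, so the change measures recovery and not response to VRE

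*Protocol article*

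**What the plan says.** All references are to the Protocol article.

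- **Timing** (Patient Recruitment and Procedure). T1 is at admission, before any intervention. The next assessment is "T2, after the VRE intervention or after CAU, in the holding area". T3 is at induction, T4 in the recovery room and T5 three days after surgery at home.
- **Pain scales** (Outcome Measures). The child's FPS-r is used at T4 and T5. For FLACC, the recovery nurse uses the "scale, will assess pain intensity at T4". The "Postoperative Pain Measure (PPPM) will be completed by parents at T5". No pain score before T4 is described.
- **Group comparison of pain** (Statistical Analyses). "repeated measures ANOVAs will be performed using postoperative pain at T4 (in the recovery room) and T5 (at home) as outcomes", with group as the between factor. Neither the scale nor the term to be tested is named.
- **Predictor regression** (Statistical Analyses). Two outcomes are set: change in child anxiety from T1 to T3, and "change in pain between T4 and T5 as outcomes". The covariates are "Predictor variables (ie, socioeconomic status, age, sex, type of surgery, preoperative child, and preoperative parental trait anxiety"). The stated purpose is "to identify which factors influence VRE efficacy".
- **Size of that regression** (Sample Size). With 6 predictors, "a sample size of 100 patients in the intervention group is sufficient".

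**The concern.** The two change scores in the regression are treated as equivalent, and they are not. T1 precedes the intervention, so T1-to-T3 change in anxiety starts from a true baseline. T4 comes after VRE and after surgery. Any effect on pain that is already present at T4 is subtracted out of the T4-to-T5 change. What remains is how fast pain resolves from its postoperative level, which is a different question from whether VRE lowered it.

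At stake is the reading of a secondary outcome for which the article states an expectation, namely less postoperative pain. A factor that goes with less pain in the recovery room could be reported as one that goes with poorer improvement, and a factor that goes with less pain throughout could be reported as irrelevant. There is also a question of fit: with three scales and two times, only one scale can supply a like-for-like change.

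**Working it through.** The article gives no figure for pain, so there is none to reproduce. The structure below follows from the document; the numerical illustrations rest on assumptions that are not in it.

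**1. Which scales allow a T4-to-T5 change**

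| Scale | T4 | T5 |
|---|---|---|
| FPS-r (child) | yes | yes |
| FLACC (nurse) | yes | no |
| PPPM (parent) | no | yes |

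Only FPS-r does.

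**2. What the regression coefficient measures.** Let a factor lower pain by a4 at T4 and a5 at T5 per SD of the factor. Its coefficient on the change (T5 minus T4) is (−a5) − (−a4) = a4 − a5, where a positive value means a smaller fall in pain.

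- Mainly early, a4 = 0.7 and a5 = 0.1: 0.7 − 0.1 = +0.6, which reads as less improvement.
- Equal at both times, 0.7 and 0.7: 0, which reads as no role.
- Larger at T5 than at T4: negative, which has the right sign.

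**3. How often this would show.** Assumptions: 100 VRE patients, 6 predictors, SD 2.5 at each time, T4–T5 correlation 0.5. The SD of the change is 2.5 × √(2 × (1 − 0.5)) = 2.5, so the slope per SD has a standard error of about 2.5/√100 = 0.25, and 0.6/0.25 = 2.4. In a simulation of 4,000 runs of the mainly early case, the change coefficient averaged about +0.61 and was significant in that direction in about 65% of runs. Regressing the T4 level on the same factor gave about −0.71, significant in about 77%.

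**4. The group comparison in the T4/T5 ANOVA.** Let b4 and b5 be the benefit of VRE at each time. The group-by-time contrast (VRE minus CAU, in change) is b4 − b5. The group main effect is −(b4 + b5)/2. With assumed means CAU 4 then 2 and VRE 2 then 1:

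- change: CAU 2 − 4 = −2, VRE 1 − 2 = −1, difference +1, which reads against VRE;
- level: −2 at T4 and −1 at T5, average −1.5, which favours VRE.

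With 100 per arm, SD 2.5 and correlation 0.3 to 0.7:

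| Benefit at T4, T5 | Difference in change | Probability that it is significant in that direction | Power of group main effect |
|---|---|---|---|
| 1, 0 | +1 | 0.67 to 0.96 | 0.34 to 0.42 |
| 1, 0.5 | +0.5 | 0.22 to 0.45 | 0.63 to 0.75 |
| 1, 1 | 0 | 0.025 (chance) | 0.87 to 0.94 |
| 0.5, 1 | −0.5 (favours VRE) | 0.22 to 0.45 | 0.63 to 0.75 |

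The same ANOVA therefore gives the right sign through its group term in every row. Its interaction term can give the wrong sign, nothing, or the right sign.

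**The case against.** A reader might infer that the plan can make an effective VRE look harmful. The documents do not support that for the regression: it lists no group term and is sized on the intervention arm, so it estimates no difference between VRE and CAU. They do not support it for the ANOVA either, as written. That model has pain levels as outcomes and group as a factor, and its group effect is a valid comparison of levels. The adverse result needs group-by-time to be read as the treatment effect, and the article never says so. The most that can be said is that the tested term is unnamed, while the primary T1/T3 ANOVA, which has the same form, must be read through its interaction to test change, so the same habit could carry over. Even then, reversal depends on a benefit that is larger at T4, and no figure in the article supports any particular pattern.

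A reader might also infer that FLACC and PPPM will be pooled across scales and raters. Nothing says this. Their timing is stated clearly, PAED at T4 gets its own ANCOVA, and a condensed article may leave the models for the two single-time scales to the full plan.

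These objections remove the headline of harm. They do not touch the regression, where the outcome and its purpose are both stated and do not match.

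**Conclusion.** The point holds for the predictor regression. T4-to-T5 change in pain cannot show which factors influence VRE efficacy, because both times follow VRE and no earlier pain score is described. This rests on the article's own timing and needs no assumed numbers. The size of the distortion does: the +0.6 coefficient and the 65% depend on the assumed SD, correlation and effect pattern, and a factor whose influence grows towards T5 would keep its correct sign.

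For the T4/T5 pain ANOVA the point is conditional. A wrong sign, or a null for a constant benefit, arises only under a group-by-time reading.

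Severity is moderate. The primary outcome (mYPAS from T1 to T3) is unaffected, and so is the group comparison of pain levels.

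**What to change.** 1. **Regression.** Replace T4-to-T5 change with FPS-r level at T4 and FPS-r level at T5. If modifiers of VRE efficacy are the question, include both arms and predictor-by-group terms. Pain levels in the VRE arm alone would identify predictors of pain, not of benefit from VRE.
2. **T4/T5 pain model.** Name FPS-r as the scale, and name the group effect on level (at each time or averaged) as the pain effect, not group-by-time. The choice should be fixed in advance. If the benefit is confined to T4, the average dilutes it (power 0.34 to 0.42 in the table), while a 1-point difference tested at T4 alone has power of about 0.80 with SD 2.5 and 100 per arm.
3. **Single-time scales.** State separate group comparisons for FLACC at T4 and PPPM at T5, in the form already planned for PAED.

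The cost is wording only, since all the data are already planned. The downside is precision. A predictor-by-group coefficient is a difference of two slopes, so with 100 per arm its standard error is about √2 × 0.25 = 0.35 under the assumptions above. A difference of 0.7 in slope then has power of about 0.51, against about 0.80 for a single-arm slope of the same size (both by normal approximation). These terms should be presented as exploratory.

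### The secondary regressions meant to show what influences VRE efficacy contain no group or group-by-factor term, so they find predictors of change, not modifiers of the VRE effect

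*Protocol article*

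**What the plan says.** Four places in the protocol article bear on this.

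- **Outcome Measures** gives the reason for measuring the factors: "Several factors associated with situational anxiety will be assessed because these may influence the efficacy of the VRE".
- **Statistical Analyses**, last paragraph, sets up multiple linear regressions for two outcomes: change in child state anxiety from T1 to T3, and change in pain from T4 to T5. The predictors are given as a closed list: socioeconomic status, age, sex, type of surgery, child trait anxiety and parental trait anxiety. They "will be included into the linear models to identify which factors influence VRE efficacy".
- **Sample Size** has a separate sentence for this analysis. It begins "To perform regression analyses with 6 predictor variables", assumes "a small to medium effect size, and a power of .85", and concludes that "a sample size of 100 patients in the intervention group is sufficient".
- **Patient Recruitment and Procedure** provides a concurrent control arm of equal size: "children will be randomly allocated to the VRE intervention (N=100) or CAU (N=100) group".

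Group is named as the between-subject variable in the repeated measures ANOVAs. It is not named in the regressions.

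**The concern.** Efficacy is a contrast between VRE and care as usual. A factor influences efficacy only if that contrast differs across its levels, so the stated purpose is a question about effect modification. The stated model has no term that carries the contrast.

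The article describes the factors as associated with situational anxiety, so some are expected to predict anxiety change whichever preparation the child receives. Such a factor could be reported as determining for whom VRE works when the VRE effect is the same for everyone. Conversely, a factor that does change the effect could go unseen. Either error could misdirect later advice on which children to offer VRE.

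**Working it through.** **1. The plan's own figure.** The effect size for the regression is given in words only. I assume Cohen's f² from 0.02 (small) to 0.15 (medium), and that the two-sided alpha of 0.05 stated for the ANOVA applies here too. Power comes from the noncentral F distribution with λ = f²·N and N − 6 − 1 denominator df.

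| Test | N for 85% power, f² = 0.02 | f² = 0.10 | f² = 0.15 | f² giving 85% at n = 100 |
|---|---|---|---|---|
| All six predictors jointly | 770 | 159 | 109 | 0.163 |
| One coefficient | 451 | 92 | 63 | 0.092 |

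The figure of 100 can be neither confirmed nor refuted. It is attainable for a single coefficient at f² of about 0.09. The point below does not depend on it.

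**2. What the model estimates.** Let a factor have slope β on change under care as usual and β + δ under VRE. Modification of the VRE effect is δ.

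- VRE arm only: the slope estimates β + δ.
- Both arms equally, no product term: the slope estimates about β + δ/2.
- Both arms with a group-by-factor term: the product coefficient estimates δ.

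Only the third isolates δ. The six listed factors match the six predictors in Sample Size, so the stated model has no place for group or a product.

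**3. False attribution, one factor.** Set δ = 0, with 100 children per arm and correlation r between factor and change. Approximate power of the one-arm slope test is Φ(√100·r/√(1−r²) − 1.96).

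| r (assumed) | √100·r/√(1−r²) | Φ(…) | Simulated, one arm | Simulated, interaction in 200 |
|---|---|---|---|---|
| 0.2 | 2.04 | 0.53 | 52% | about 5% |
| 0.3 | 3.14 | 0.88 | 86% | about 5% |
| 0.4 | 4.36 | 0.99 | 99% | about 5% |

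**4. The six-factor model.** This simulation used 4,000 runs, 100 children per arm, six independent standard normal factors, and a slope of √0.0927 = 0.304 on one of them (residual SD 1).

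| True state | VRE arm only | Pooled, no group or product term | Interaction test |
|---|---|---|---|
| Same slope in both arms (no modification) | 82% | 98% | 5% |
| Slope under care as usual only (true modifier) | 5% | 53% | 54% |

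The one-arm model flags the non-modifier in most runs and finds the true modifier only at the chance rate. Pooling without a product term does not cure the first error.

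**5. Price of the right test.** The standard error of a slope difference between two arms of 100 is √2 times that of one arm's slope. With slope 0.304:

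- one arm: Φ(3.04 − 1.96) = 0.86;
- difference: Φ(3.04/√2 − 1.96) = Φ(0.19) = 0.58, and 0.54 in the six-factor simulation.

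Restoring about 85% for that difference needs about 200 per arm, since √(2/200) = √(1/100).

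**The case against.** **The analysis set is not stated.** Correct. Statistical Analyses does not restrict the regression to the VRE arm. A reader might take the one-arm analysis as declared, but it is inferred from the sizing sentence. The point survives either reading, because the pooled model without a product term also cannot isolate modification.

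**An article condenses the full protocol.** This would answer a complaint about missing detail. Here the purpose, the predictors and the sizing sample are all stated, and they do not fit together. An analysis plan would have to change the stated model, not just add to it.

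**The percentages are power for a real association.** This stands in part. The 52% to 99% assume that a prognostic factor of that strength exists, and the article gives no such correlations. The result becomes a false statement only when the slope is read as influence on efficacy. So the plan may, not must, produce false claims.

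**Change without T1 as covariate.** A reader might add that omitting T1 anxiety is a further error because of regression to the mean. The document does not support that. With equal variances at T1 and T3, the correlation of a factor with change is (q₃ − q₁)/√(2(1 − r)), where q₁ and q₃ are its correlations with T1 and T3 and r is the T1–T3 correlation. If the factor acts only through T1 with q₁ = 0.3, this is −0.177 at r = 0.3 and −0.150 at r = 0.5. If it relates equally to T1 and T3, it is zero. The inputs are not in the article, and for non-randomised predictors the two models answer different questions.

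**Conclusion.** The concern holds as a mismatch between a stated model and its stated purpose, for both the anxiety and the pain regression. As written, the analysis identifies predictors of change and cannot tell them from modifiers of the VRE effect. That conclusion is structural and needs no assumed effect size. Its practical size does: about 52% to 99% false attribution for a prognostic factor correlated 0.2 to 0.4 with change, against about 5% for an interaction test.

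Severity is moderate. A reader might infer that a main aim of the trial cannot be met, but the Objective and the end of the Introduction set the aims as developing the tool and testing it against care as usual. Identifying who benefits is not among them. This is a secondary analysis, and the primary VRE-versus-care-as-usual comparison is untouched.

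**What to change.** Either of two changes resolves the mismatch.

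1. **Keep the question, change the model.** For both outcomes, fit all 200 children with group, the six factors and prespecified group-by-factor terms. Use a joint test of the products, or single terms with multiplicity acknowledged: six independent tests at 5% give 1 − 0.95⁶ = 26% chance of at least one false positive, and twelve over both outcomes give 1 − 0.95¹² = 46%. Base any statement about VRE efficacy on the interaction estimates and their confidence intervals, and call it exploratory. Including T1 mYPAS in the anxiety model is optional. T4 pain should not be treated as a baseline, because it is measured after randomisation.
2. **Keep the model, change the claim.** Describe the analysis as predictors of change in VRE-treated children, say explicitly that it uses that arm only, and drop the efficacy wording.

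Neither option needs more patients or measurements: assessments are planned for both arms, and recruitment was still open when the article was written. The cost of the first is the lower power shown above (about 54–58% where the one-arm slope has about 85%), so a null interaction must not be read as evidence that VRE works equally for all. The cost of the second is that the question of who benefits is left unanswered.
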